### Biobank

For the measurements and analysis of some outcomes, a biobank is established in which the separated plasma/serum and urine samples are allocated in separate micro-tubes and stored in an ultra-low temperature freezer with the patient’s dedicated code. Based on the regulations of the local data protection agency, after the measurements, all the remaining samples will be anonymized and the biobank will be discontinued. All patients are informed in the consent form about the establishment of the biobank.

### Study monitoring

Monitoring the study and data source verification is the responsibility of the Research Council of Zanjan University of Medical Sciences, Iran which is independent from the study sponsors and any potential competing interests. All the forms used in this study, including the consent form, trial procedure manual, trial violation form, adverse events form, and outcomes’ related checklists, were evaluated and validated by a team of clinical trial monitors and the above Council. Recruitment visits are conducted under direct observation of the team. Human subject de-identification is an issue which is considered as local/regional and national requirements among all presentations and publications. To fulfill that requirement, appropriate measurements such as encoding or deletion are enforced. All of the study investigators are informed to follow the trial procedure manual. Also, any deviation from the protocol by any investigator will be recorded into the trial violation form designed by the Ethics Committee of the Zanjan University of Medical Sciences. All of the study forms are in the Persian language.

### Adverse event recording

Any adverse events, related or unrelated, whether reported by the patient or discovered by the investigators during the study follow-up (until week 28) will be recorded in the adverse events form. At the same time, the Research Council of the Zanjan University of Medical Sciences will be notified at the time of the recording. The severity and the importance of the adverse events for further decisions (e.g. discontinuation, unblinding, etc.) will be evaluated by a physician. In case of occurrence of any adverse event, patient/s will be completely followed up by the assigned physician/s and the treatment charges will be fully covered by the trial team. The standard adverse event form is presented in the Additional file 1.

### Potential confounding factors

According to the nature of the variables in primary and secondary outcomes, two potential major study confounding factors were predicted: (1) patients’ nutritional status and (2) patients’ physical activity status. To evaluate the impact of these possible confounding factors, the food frequency questionnaire (FFQ) and the physical activity questionnaire (FAQ) are used. The forms are filled at the day of recruitment. Also, patients are advised not to change their routine diet or physical activity during the study.

### Statistical considerations

#### Sample size calculations

The sample size was estimated based on the changes in plasma IL-6 level as a primary outcome of treatment. According to a previous study, the SGLT2-i dapagliflozin reduced the mean plasma IL-6 level from 6.6 to 5.8 (pg/mL) with the standard deviation (SD) of 8.9 [17]. The minimal important difference (MID) of the IL-6 level was calculated 4.45 (pg/mL) using 0.5 × SD (the distributional-based method) [18]. With a study power of 80%, an alpha level of 0.05%, and MID of 4.45, the required sample size was calculated to be 41 patients in each arm. Considering a 20% dropout during the study, the sample size was rounded up to 50 participants in each arm. The sample size was calculated using the G-power software (version 3.1.9.2).

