#### Statistical analysis plan

We will use the means ± standard deviations (SD) and frequencies and percentages n (%) to interpret the results. The noninferiority margin and 95% confidence interval (CI) will be estimated for primary outcomes. The noninferiority will be accepted if the upper 95% CI for the relative risk (RR) lies below the margin of noninferiority. An intention-to-treat analysis will be used to examine the effect of missing data. Superiority analysis will be performed at α = 0.05 level. The interaction effects will be examined using graphical and statistical tests. The Kolmogorov–Smirnov test will be used to determine the normality of the distribution of continuous quantitative data. Independent T-test will be used (on condition of normal distribution) for statistical analysis of quantitatively continuous variables findings related to primary and secondary outcome including interleukin 6 levels, oxidative stress biomarkers, platelet function, glycemic status, cardiac biomarkers, echocardiographic finding, hematopoietic and renal biomarker, lipid profile and electrocardiographic parameters. The Mann–Whitney U test will be used on the condition of abnormal distribution. Chi-square test will be used to analyze qualitative data such as ST segment deviation and T-wave changes in electrocardiogram. We will consider the probability of 0.05 for the main analysis. We will perform Bayesian analysis of the covariance test to examine the effects of intervention on IL-6. The primary outcome is considered as confirmatory and the secondary outcomes are considered as exploratory. All statistical tests will be carried out in the in Rv.4 environment. The primary data of the FFQ will be evaluated by using the Nutritionist software version 4 (N4).

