## Discussion

The EMPA-CARD randomized placebo-controlled clinical trial seeks to investigate the mechanisms underlying the cardiovascular effects of empagliflozin in patients with T2DM who have proven CAD at the same time.

Most of the recent published clinical trials have focused on the effects of empagliflozin in patients with heart failure in which the superiority of empagliflozin has been reported. The recent meta-analysis with the pooled population of 8474 patients (DAPA-HF and EMPEROR-Reduced population) showed that treatment with an SGLT2-i was associated with a significant reduction in cardiovascular death (pooled hazard ratio of 0.86) and re-hospitalization due to heart failure complications as well as improvements in renal function [19]. However, limited data are available regarding the beneficial effects of empagliflozin in patients with established CAD. The EMPA-HEART Cardiolink-6 trial showed that 6 months of treatment with empagliflozin significantly reduced left ventricular mass index (LVMi) in patients with T2DM and CAD [20]. In this study we are exploring molecular mechanisms and cellular changes that potentially mediate these beneficial effects. Plasma levels of IL-6, a pro-inflammatory cytokine which also has anti-inflammatory properties promotes and regulates inflammatory processes in patients with T2DM, and changes in its level is considered as the primary outcome of this study. The rationale of choosing this biomarker as a leading factor for investigation among other candidates is that IL-6 and tumor necrosis factor-alpha (TNF-α) appear to have the highest impact on the promotion of CAD in patients with diabetes mellitus [21]. Moreover, the other factors measured in this study are either directly or indirectly affected by IL-6. It has been shown that IL-6 reduces oxidative stress and apoptosis of pancreatic β-cell by promoting autophagy, an adaptive response to cellular stress. Previous human studies have shown that concomitant treatment with empagliflozin and metformin in patients with type 1 diabetes reduced IL-6 up to 1.34 fold and improved anti-oxidative status parameters comprising of total anti-oxidative status (TAS) for up to 1.07 fold and superoxide dismutase (SOD) for up to 1.08 fold. It has also been suggested that the cardio-protective effects of this drug class may be associated with its anti-oxidative effects, including normalizing interferon-γ (IFN-γ), TNF-α and IL-6 levels especially with empagliflozin [22, 23]. In animal studies, diabetic rats which were treated by SGLT2 inhibitor had a lower development of endothelial dysfunction, oxidative stress, advanced glycation end products/ receptor for advanced glycation end products (AGE/RAGE) signaling and inflammation due to inhibition of the activity of NADPH oxidase and decreased serum levels of the AGE precursor methylglyoxal [24]. In a study by Tahara et al. diabetic rats which were treated by ipragliflozin had significantly lower plasma levels of IL-6, TNF-α, monocyte chemoattractant protein-1 (MCP-1), and CRP [25]. Nevertheless, it seems that the inflammation and fatty acid oxidation, which are also promoted by IL-6, have greater impact on increasing the oxidative stress in patients with T2DM. This could enhance the rate and magnitude of coronary atherosclerosis and subsequent CAD [26, 27].

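### The stated inputs do not give 41 patients per arm: they need 64, and the planned trial has about 60% power, not 80%

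*Protocol article*

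**What the plan says.** All the sizing inputs are in the protocol article under "Sample size calculations", a single paragraph.

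- Endpoint: "The sample size was estimated based on the changes in plasma IL-6 level as a primary outcome of treatment".
- Source of the SD: an earlier dapagliflozin study that "reduced the mean plasma IL-6 level from 6.6 to 5.8 (pg/mL) with the standard deviation (SD) of 8.9".
- Target difference: "The minimal important difference (MID) of the IL-6 level was calculated 4.45 (pg/mL) using 0.5 × SD".
- Result, after a stated power of 80%: "alpha level of 0.05%, and MID of 4.45, the required sample size was calculated to be 41 patients in each arm".
- Dropout: "Considering a 20% dropout during the study, the sample size was rounded up to 50 participants in each arm".

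The section headed Statistical analysis plan names the independent t-test, or Mann–Whitney U if the data are not normal. It says "Superiority analysis will be performed at α = 0.05 level". It makes IL-6 the confirmatory outcome. The abstract gives 1:1 allocation. The sizing paragraph does not state sidedness, a baseline-to-week-26 correlation, or whether 8.9 is the SD of IL-6 levels or of their change.

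**The concern.** When the target is defined as half an SD, the SD cancels and the standardised effect is 0.5 whatever the units. The usual two-sample answer for 0.5 at two-sided 5% and 80% power is in the sixties per arm, so 41 looked too low by about a third. The alpha printed with a percent sign and a dropout allowance that ends below the required number suggested that the paragraph had not been checked.

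IL-6 is the only confirmatory outcome. If the power is 60% and not 80%, the trial misses its own target difference about 40% of the time, and a reader relying on the stated power would take a non-significant result as stronger evidence against an effect than it is. The target is also large for a difference called minimal: 4.45 is 67% of the quoted baseline mean (4.45/6.6) and 5.6 times the fall quoted in the same paragraph (4.45/0.8, where 0.8 = 6.6 − 5.8).

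**Working it through.** **Inputs.** Difference 4.45 pg/mL, SD 8.9 pg/mL and power 80% (Sample size calculations); alpha 0.05 and independent t-test (Statistical analysis plan); 1:1 allocation (abstract). Two-sided testing is assumed, in line with the planned 95% confidence interval; one-sided is also shown.

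**Standardised effect.** d = 4.45/8.9 = 0.5.

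**Attempt to reproduce 41.** By the normal approximation, n per arm = 2(z₁₋α/₂ + z₀.₈)²/d² = 2(1.960 + 0.842)²/0.25 = 62.8, so 63. The noncentral t distribution gives the exact t-test figures below.

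| Reading of the stated inputs | n per arm for 80% power |
|---|---|
| Two-sided alpha 0.05 | 63.8, so 64 |
| One-sided alpha 0.05 | 50.2, so 51 |
| Two-sided, alpha as printed (0.05% = 0.0005) | 152.5, so 153 |
| Two-sided 0.05, Mann–Whitney U | 67 (normal data) to 74 (least favourable distribution) |

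None of these gives 41. A one-sided 10% test gives 37, and a paired t-test at two-sided 0.05 gives 34 in total; neither matches.

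**Power of the planned trial for 4.45 pg/mL (t-test, alpha 0.05).**

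| Evaluable per arm | Two-sided | One-sided |
|---|---|---|
| 40 (50 less 20%) | 59.8% | 71.6% |
| 41 | 60.9% | 72.6% |
| 50 (no dropout) | 69.7% | 79.9% |

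**Detectable difference, 80% power, two-sided 0.05.**
- 40 per arm: d = 0.634, and 0.634 × 8.9 ≈ 5.6 pg/mL.
- 50 per arm: d = 0.566, and 0.566 × 8.9 ≈ 5.0 pg/mL.

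**Dropout.** To keep 41 completers at 20% loss needs 41/(1 − 0.20) = 51.25, so 52 per arm. The plan's 50 is close to 41 × 1.20 = 49.2 rounded up, and leaves 50 × 0.80 = 40. With 64 as the required number, the randomised number would be 64/0.80 = 80 per arm.

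**Alpha.** Taken literally, 0.05% gives about 9% power at 40 per arm and 10% at 41. The analysis section gives 0.05, so this is almost certainly a slip and the main result does not rest on it.

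**Could an unstated correlation explain 41?** Suppose 8.9 is the SD of levels and ρ is the baseline-to-week-26 correlation. The SD is then 8.9√(2(1 − ρ)) for a change score and 8.9√(1 − ρ²) for analysis of covariance (ANCOVA). With 41 per arm, 80% power needs d = 0.626, that is an SD of 4.45/0.626 = 7.1. That requires ρ ≈ 0.68 for change scores or ρ ≈ 0.60 for ANCOVA. Two-sided power at 40 per arm, with ρ an assumption throughout:

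| ρ | Change score | ANCOVA |
|---|---|---|
| 0.3 | 46% | 64% |
| 0.5 | 60% | 72% |
| 0.7 | 81% | 87% |

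**Effect of the size the paragraph quotes.** For 0.8 pg/mL, d = 0.8/8.9 = 0.09, and two-sided power at 40 per arm is about 7%.

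**The case against.** The strongest reply is that 60% depends on one reading of an incompletely specified calculation: two-sided, unadjusted, 8.9 taken as the SD of the analysed quantity, and the full 20% lost. With 50 evaluable per arm and a one-sided test, power is almost exactly 80%. The analysis section also mentions a Bayesian analysis of covariance for IL-6. If 8.9 is the SD of levels, adjustment at a correlation of 0.6 or more would bring 41 per arm to about 80%.

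Part of this stands. True power depends on quantities the article does not give, and an adjusted analysis could do better than 60%. None of it rescues 41 as the consequence of the stated inputs. One-sided testing still needs 51 per arm and gives only 72–73% at 40–41. The sizing paragraph mentions neither a correlation nor an adjusted analysis, and a change-score analysis at ρ = 0.3 does worse than 60%. Nor is this detail that an article leaves to a fuller document: inputs and result are both printed, and they disagree.

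It is also fair to say that the alpha misprint is a typing slip, that the dropout shortfall is one patient per arm (about one percentage point of power), and that the half-SD target is openly described as distribution-based. These are secondary. Finally, the protocol does not say that a null result will be read as no effect, and it already plans a confidence interval; the concern is what a reader will infer from a stated 80%.

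**Conclusion.** The sample size statement is wrong as written. From the stated SD, difference and power, with the alpha and test in the analysis section, the requirement is 64 per arm two-sided, against 41: a shortfall of 23 evaluable patients per arm. Two-sided power for 4.45 pg/mL is about 60% after the planned dropout and at most 70% with none. This assumes an unadjusted two-sample t-test with 8.9 as the SD of the analysed quantity. One-sided testing does not reproduce 41 either. Only an undisclosed baseline correlation of about 0.60 (ANCOVA) or 0.68 (change score), or an SD near 7.1, would. The alpha misprint and the dropout arithmetic are separate, smaller errors in the same paragraph.

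**What to change.** Keep 50 per arm; 91 patients were already randomised when the article was written, and the correction needs no more. In the sample size paragraph:

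1. Correct alpha to 5%, two-sided, to agree with the analysis section, and name the test.
2. Say whether 8.9 is the SD of levels or of change. If a baseline correlation was used to reach 41, state its value and source.
3. If none was used, replace the 80% claim with power of about 60% (40 evaluable per arm) to 70% (50 evaluable) for 4.45 pg/mL, or state that 80% power applies to 5.0–5.6 pg/mL.
4. Correct the dropout step: 50 randomised per arm leaves 40 evaluable at 20% loss.
5. State that a non-significant IL-6 result will be reported with its confidence interval and described as inconclusive, not as absence of effect.

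Calling 4.45 the planning difference instead of the minimal important difference would help the reader but is optional.

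The cost is one rewritten paragraph and a less favourable stated power.

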#### Statistical analysis plan

We will use the means ± standard deviations (SD) and frequencies and percentages n (%) to interpret the results. The noninferiority margin and 95% confidence interval (CI) will be estimated for primary outcomes. The noninferiority will be accepted if the upper 95% CI for the relative risk (RR) lies below the margin of noninferiority. An intention-to-treat analysis will be used to examine the effect of missing data. Superiority analysis will be performed at α = 0.05 level. The interaction effects will be examined using graphical and statistical tests. The Kolmogorov–Smirnov test will be used to determine the normality of the distribution of continuous quantitative data. Independent T-test will be used (on condition of normal distribution) for statistical analysis of quantitatively continuous variables findings related to primary and secondary outcome including interleukin 6 levels, oxidative stress biomarkers, platelet function, glycemic status, cardiac biomarkers, echocardiographic finding, hematopoietic and renal biomarker, lipid profile and electrocardiographic parameters. The Mann–Whitney U test will be used on the condition of abnormal distribution. Chi-square test will be used to analyze qualitative data such as ST segment deviation and T-wave changes in electrocardiogram. We will consider the probability of 0.05 for the main analysis. We will perform Bayesian analysis of the covariance test to examine the effects of intervention on IL-6. The primary outcome is considered as confirmatory and the secondary outcomes are considered as exploratory. All statistical tests will be carried out in the in Rv.4 environment. The primary data of the FFQ will be evaluated by using the Nutritionist software version 4 (N4).

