## Background

Diabetes mellitus (DM) is a chronic disease that is characterized by high blood glucose levels due to the inability to produce adequate amounts of insulin and/or resistance to the hormone’s actions [1]. Type 2 diabetes mellitus (T2DM) is a complex metabolic condition and, as the most common type of diabetes, it affects some 37% of the population in western and middle-eastern societies leading to long-term complications [2]. The major complications of this disease fall into two general categories of microvascular and macrovascular involvements, which can consequently lead to cardiovascular, neurological, ophthalmological, and renal damage [3]. Cardiovascular complications are the leading cause of death in the affected population. Atherosclerosis develops more rapidly in these patients and increases the incidence of a heart attack two to three times [4]. The management methods require multi-faceted strategies, including regular physical activity, proper diet, and medications to control hyperglycemia, hypertension, inflammation, and dyslipedemia [5, 6]. Among various medications available to treat diabetes, one of the newest ones is sodium-glucose co-transport 2 inhibitors (SGLT2-i) including empagliflozin, dapagliflozin, and canagliflozin. Empagliflozin is a selective inhibitor of the SGLT2 co-transporter expressed in the proximal tubule of nephrons. Inhibition of SGLT2 reduces hyperglycemia by decreasing glucose reabsorption in the kidneys leading to increased urinary glucose excretion, reductions in blood glucose and HbA_1C_ [7]. The EMPA-REG OUTCOME trial and its sub-studies revealed the additional beneficial effects of this medication versus standard treatment protocols in patients with T2DM and heart failure. These effects include a reduction in Major Adverse Cardiovascular Events (MACE), blood pressure, urinary albumin exertion, and improvements in lipid profile and vascular resistance [8, 9]. Some hypotheses have been advanced to explain the beneficial cardiovascular effects of this agent including hemodynamic changes due to decreased plasma volume following glycosuria-induced diuresis, changes in heart fuel consumption, improvements in overall metabolism by a reduction of inflammation, and direct effects on the cardiac tissue; however, the underlying mechanisms remain obscure [10, 11]. Many factors contribute to the physiopathology of cardiovascular complications in patients with T2DM including an increase in pro-inflammatory factors, imbalance in oxidative stress and a hyper-coagulation state with abnormal platelet function [12]. In this regard, animal models and in-vitro studies have been performed to evaluate the effects of empagliflozin on inflammatory state and platelet function. The results showed a reduction in oxidative stress, pro-inflammatory phenotype, and glucotoxicity, but platelet function remained unchanged [13, 14]. To date, few human model randomized trial has been performed to evaluate the inflammation and platelet dysfunction hypothesis in T2DM patients with coronary artery disease (CAD). Hence, the main objective of this parallel group, triple-blind randomized placebo-controlled trial is to test the hypothesis that empagliflozin improves the inflammatory state in T2DM patients with documented known CAD.

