
## Methods and experimental design

### Study design and Intervention

EMPA-CARD is a multicenter triple-blind randomized placebo-controlled trial designed to evaluate the effect of treatment with empagliflozin (10 mg tablet once daily) versus placebo for 26 weeks, in addition to standard care, in patients with T2DM and coronary artery disease.

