#### Primary outcome

The primary outcome of this study is the changes in plasma interleukin 6 levels after 26 weeks of the treatment between the two study arms.

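### The analysis plan attaches to the continuous primary outcome a noninferiority rule on a relative risk that cannot be computed, beside superiority analyses, without saying which decides

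*Protocol article*

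**What the plan says.** **Question and design.** The Background sets out to "test the hypothesis that empagliflozin improves the inflammatory state in T2DM patients with documented known CAD". Study design and Intervention describes empagliflozin "versus placebo for 26 weeks, in addition to standard care, in patients with T2DM and coronary artery disease".

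**Endpoint definition.** "The primary outcome of this study is the changes in plasma interleukin 6 levels after 26 weeks of the treatment between the two study arms". Table 4 gives the measurement as an ELISA at weeks 0 and 26. No threshold, responder or event is defined for IL-6.

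**Decision rule.** The Statistical analysis plan section says "The noninferiority margin and 95% confidence interval (CI) will be estimated for primary outcomes", and then "The noninferiority will be accepted if the upper 95% CI for the relative risk (RR) lies below the margin of noninferiority".

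**Other analyses in the same section.** "Superiority analysis will be performed at α = 0.05 level". Also: "Independent T-test will be used (on condition of normal distribution) for statistical analysis of quantitatively continuous variables findings related to primary and secondary outcome", with IL-6 named in the list that follows and the Mann-Whitney U test as the fallback. A Bayesian analysis of covariance on IL-6 is added. The primary outcome is called confirmatory and the secondary outcomes exploratory.

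**Sample size.** This section works from a minimal important difference of 4.45 pg/mL and an SD of 8.9 pg/mL. It contains no noninferiority margin and no event rate.

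**The concern.** The noninferiority rule conflicts with the rest of the article in four ways.

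- **Scale.** A relative risk needs a binary outcome. The only qualitative outcomes named in the analysis section are ECG findings, and those are secondary outcomes meant for sub-studies.
- **Question.** Showing that a drug is not much worse than placebo does not show that it improves inflammation.
- **Margin.** It has no value and no unit, and the text says only that it will be estimated. A margin must be fixed before the data are seen.
- **Sizing.** The trial was sized on a difference in means.

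At stake is the clarity of the one confirmatory result. The rule cannot be applied as printed. Anyone who wanted to apply it would have to choose a scale and a margin afterwards. The superiority sentence does not settle this, because nothing ranks the superiority analysis, the t-test or Mann-Whitney test, the Bayesian model and the noninferiority rule. If superiority were not shown, the published text would still leave a second, undefined claim open.

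**Working it through.** **1. Can the rule be computed as written?** It needs a relative risk for the primary outcome. The Primary outcome section defines "changes in plasma interleukin 6 levels after 26 weeks of the treatment between the two study arms", a difference in a concentration. Table 1, Table 4 and the abstract agree and add no dichotomy. The rule therefore has no input.

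**2. Does the sample size imply a noninferiority design?** The stated result is 41 per arm, from a difference of 4.45, SD 8.9 and 80% power. I read alpha as 0.05; the Sample size section prints 0.05%, the analysis section 0.05. For a comparison of two means:

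n per arm = 2 × (1.960 + 0.842)² / (4.45/8.9)² = 2 × 7.85 / 0.25 = 62.8, so 63 two-sided (64 by exact t-test). One-sided it is 50 (51 by exact t-test).

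The stated 41 does not reproduce, which is a separate matter. What counts here is that the inputs are a mean difference and an SD, with no margin and no event rate. Below, 41 and 50 per arm serve only as the plan's own evaluable and randomized numbers.

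**3. What would an open margin permit?** This step is conditional. It assumes that the rule is moved to the mean difference in IL-6 (drug minus placebo, higher is worse), that SD 8.9 applies, and that the true difference is zero. Noninferiority is accepted when the upper 95% limit lies below the margin M:

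SE = 8.9 × √(2/n), which is 1.966 at n = 41 and 1.780 at n = 50.

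P(accept | no effect) = Φ(M/SE − 1.96).

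Example with M = 4.45: at n = 41, Φ(2.264 − 1.96) = Φ(0.304) = 0.62. At n = 50, Φ(2.50 − 1.96) = Φ(0.54) = 0.71.

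| Assumed margin (pg/mL) | Origin of the figure | n = 41 | n = 50 |
|---|---|---|---|
| 0.8 | earlier dapagliflozin change, 6.6 − 5.8 | 6.0% | 6.5% |
| 2.225 | half of 4.45 | 20% | 24% |
| 4.45 | the protocol's minimal important difference | 62% | 71% |
| 8.9 | one SD | over 99% | over 99% |

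Under a two-sided superiority test at 0.05, an inert drug is declared better in 2.5% of trials, whatever n is. As M falls to zero the formula gives Φ(−1.96) = 2.5%, so the rule then becomes the superiority test.

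**4. The same on a relative-risk scale.** Suppose instead that IL-6 were dichotomised, which the plan does not propose, with the same risk in both arms. Simulation (200,000 draws, 41 per arm, Wald interval on the log scale) gives these acceptance rates for an inert drug as the assumed risk rises from 30% to 70%: 9 to 35% at a margin of 1.25, 23 to 79% at 1.5, and 54 to 99% at 2.0. The choice of scale therefore matters as much as the choice of margin.

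**The case against.** The strongest reply is that the plan does test superiority. The same section announces a superiority analysis at 0.05, assigns IL-6 to a t-test or Mann-Whitney test, sets 0.05 for the main analysis and adds a Bayesian analysis of covariance. On this view the noninferiority lines are stray text and do no harm. The first half stands: a valid superiority analysis is there. The second half does not, because the stray rule is addressed to the primary outcome, is the only sentence with an explicit acceptance criterion on an effect measure, and is not ranked below anything.

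A reader might infer more: that the trial is judged by noninferiority, so that an inert drug could be declared a success. The documents do not support that. They say when noninferiority would be accepted, never that acceptance is success, and they frame the hypothesis as improvement throughout. As printed, the rule cannot accept anything, because its relative risk does not exist. The inert-drug risk needs three further steps that are not in the text: a new scale, a margin looser than no difference, and noninferiority reported as efficacy.

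Two smaller objections also stand. An estimated margin need not mean one derived from the trial data; what can be said is that none is fixed. And SD 8.9 is quoted beside mean levels, not stated as the SD of change. A smaller SD would raise the acceptance rates at every margin, and a larger one would lower them.

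It could also be said that an article leaves detail to a fuller plan. This is not missing detail, however. It is a stated rule that contradicts the article's own outcome, hypothesis and sample size.

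**Conclusion.** The rule is wrong as written and should be removed. It cannot be applied to IL-6, does not fit a placebo-controlled improvement question and has no margin. It stands beside valid superiority analyses with nothing to say which of them decides the confirmatory result.

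The effect on error rates is conditional and cannot be reduced to one figure. With the rule rebuilt on the mean difference and reported as success, the chance that an inert drug passes runs from about 6% to over 99% for margins of 0.8 to 8.9 pg/mL, against 2.5% under superiority. The margins are assumptions, as is the use of SD 8.9 for the change. That spread is a measure of how much an unspecified margin leaves open; it does not predict what this trial will do.

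**What to change.** Make a dated change before unblinding. The article reports 91 patients randomized by 9 November 2020, so the change should be recorded as made without knowledge of results by arm.

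- Delete both sentences on noninferiority and relative risk.
- State that the primary hypothesis is superiority of empagliflozin over placebo in IL-6 change at week 26, tested two-sided at alpha 0.05 and reported as a between-arm difference with its 95% CI.
- Name one analysis as confirmatory. Baseline-adjusted analysis of covariance is one option, since baseline IL-6 is already measured. The defect does not dictate this choice, but a choice has to be made.
- Label the remaining IL-6 analyses (t-test or Mann-Whitney, and Bayesian, unless one of them is the analysis named) as supportive.

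The cost is a short rewrite of the analysis section plus documentation of the change. It needs no new data, visits or patients.

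### A normality pre-test on the trial's own data decides whether the confirmatory IL-6 analysis compares means or ranks, so the primary test and estimand are not fixed in advance

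*Protocol article*

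**What the plan says.** The article defines its confirmatory endpoint in the Outcomes section as follows: "The primary outcome of this study is the changes in plasma interleukin 6 levels after 26 weeks of the treatment between the two study arms".

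Under Statistical analysis plan, the Kolmogorov–Smirnov "test will be used to determine the normality of the distribution of continuous quantitative data". If the distribution is judged normal, an independent t-test is used; otherwise the Mann–Whitney "U test will be used on the condition of abnormal distribution". The list of variables under this rule names IL-6 levels. The same section adds a Bayesian analysis of covariance for IL-6 and calls the primary outcome confirmatory. It does not say which of these analyses decides the trial. It also does not say whether normality is checked on the level or the change, in each arm or pooled, or with which critical values.

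Under Sample size calculations, the planning study of dapagliflozin is said to have "reduced the mean plasma IL-6 level from 6.6 to 5.8 (pg/mL) with the standard deviation (SD) of 8.9". Half of that SD, 4.45 pg/mL, is the difference for which the trial is sized.

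**The concern.** A t-test estimates a difference in mean change in pg/mL, the quantity behind the 4.45. Mann–Whitney asks whether values in one arm tend to be lower than in the other. These are different questions, and under skew they can give different answers from the same data. A confirmatory analysis should settle the question before the data are seen. Here a goodness-of-fit test on the outcome data settles it, and a third, unranked analysis sits beside the other two.

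The planning figures gave warning. An SD larger than the mean of a quantity that cannot be negative suggests strong right skew, and a log-scale analysis could have been fixed at the design stage. The article states the selection rule itself, so this is a rule badly fixed rather than a detail left to a fuller document.

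**Working it through.** **Inputs from the article.** Mean IL-6 6.6 and 5.8 pg/mL, SD 8.9, target difference 4.45, 41 per arm before dropout and 50 after (Sample size calculations); α = 0.05 (Statistical analysis plan).

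**Inputs assumed.** IL-6 is lognormal; 8.9 is the SD of the level; the baseline to week-26 correlation on the log scale is 0.3–0.8; treatment acts as a proportional reduction.

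**1. The plan's own target.** 0.5 × 8.9 = 4.45, so the standardised difference is 4.45/8.9 = 0.5. This is a difference in means and corresponds to the t-test branch only. The 41 per arm is used below simply as the number analysed. It does not reproduce from these inputs (a two-sided two-sample t-test with 80% power needs 64), but that is a separate matter.

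**2. Shape of the level.** Under a normal curve with SD 8.9, the share below zero is:
- mean 6.6: 6.6/8.9 = 0.742, Φ(−0.742) = 22.9%
- mean 5.8: 5.8/8.9 = 0.652, Φ(−0.652) = 25.7%

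The matching lognormal has σ = √ln(1 + (8.9/6.6)²) = 1.018 and median 3.93.

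**3. Which test the rule selects.** Share of simulated null trials sent to Mann–Whitney, 41 or 50 per arm:

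| Variable tested | Version of Kolmogorov–Smirnov | Mann–Whitney chosen |
|---|---|---|
| Change | plain critical values, either arm fails | 65–87% |
| Change | plain critical values, pooled | 81–96% |
| Change | Lilliefors correction | 98–100% |
| Level | any of these | 90–100% |

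If the change is instead symmetric with moderately heavy tails (t with 4–10 degrees of freedom), normality is rejected in under 1% to 51% of trials, depending on the version.

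**4. Type I error.** 4.2–5.2% for the two-stage rule.

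**5. Disagreement.** For the change in IL-6, the t-test and Mann–Whitney differ on significance in about 5% of null trials. With a sizeable effect (reductions of 30–67%) they differ in roughly 17–28%.

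**6. Power.** Change in IL-6, 41 per arm, correlation 0.5–0.7, plain Kolmogorov–Smirnov with either arm failing. The article gives no proportional effect except by implication: (6.6 − 5.8)/6.6 = 12% and 4.45/6.6 = 67%. The 40% is an assumed middle value.

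| Reduction | Two-stage rule | ANCOVA on log IL-6 |
|---|---|---|
| 12% | 7–9% | 10–12% |
| 40% | 40–60% | 73–87% |
| 67% | about 90–98% | about 100% |

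At a 40% reduction and correlation 0.5 the steps are: t-test on change 28–30%, two-stage rule 40%, Mann–Whitney on change 43–44%, t-test on log change 61%, ANCOVA on log IL-6 72–73%. Simulation error is one to two percentage points.

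**The case against.** **The zero bound concerns the level, not the endpoint.** A change can be negative, and the text does not exclude that 8.9 is the SD of the change. A reader might infer that the plan's figures prove the primary endpoint cannot be normal. They do not. This stands. It weakens the skew argument but not the objection to selecting the confirmatory test from the data.

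**The choice is less random than it looks.** A reader might infer that the primary test is left to chance. With skew as strong as assumed, the Lilliefors version, or testing the level, sends nearly every trial to Mann–Whitney. Only plain critical values on the change leave the choice substantially open. This also stands, but the article does not say which version applies, and the near-certain branch is the one that does not match the sample-size target.

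**The pre-test itself costs little.** Two-stage power (40%) is close to that of Mann–Whitney fixed in advance (43–44%), and type I error is not materially inflated. Most of the gain comes from the log scale and baseline adjustment, on data generated as lognormal. This is correct. The power gap shows that a better analysis is available; it is not the price of the pre-test.

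**An effect estimate may be intended.** A reader might infer that the Mann–Whitney branch would leave a p-value with no estimate. The article promises a 95% confidence interval for primary outcomes, and the estimate that accompanies a rank test may be left to a fuller plan. That stronger reading is not supported.

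**Conclusion.** The point holds in limited form. The primary test and estimand for IL-6 depend on the trial data, and three analyses are named without a hierarchy. This follows from the text and needs no simulation.

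The size of the harm does rest on assumptions: a lognormal shape, 8.9 as the SD of the level, a log-scale correlation of 0.5–0.7 and a proportional effect. Under these, the power loss against ANCOVA on log IL-6 is about 27–33 percentage points at a 40% reduction (73 − 40 = 33; 87 − 60 = 27). It is small at a 67% reduction, where every option is strong, and at a 12% reduction, where none has useful power. Non-normality of the change is not proved, and false-positive inflation is not part of the finding.

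**What to change.** - Remove the normality pre-test as a selector of the primary analysis.
- Name one primary analysis: ANCOVA of log week-26 IL-6 on treatment and log baseline IL-6, with the ratio of geometric means and its 95% CI.
- Label Mann–Whitney (with the Hodges–Lehmann shift) and the Bayesian analysis of covariance as sensitivity or supportive analyses.
- Use the same log-scale approach for the other positive, skewed biomarkers, such as hs-CRP and IL-1b.

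The cost is a change of wording, to be made before unblinding. The effect is then reported as a percentage rather than in pg/mL, so the 4.45 pg/mL target would need restating on that scale. A fixed rule is also needed for values below the detection limit.
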